**Methods and analysis:**

This study will be an explanatory mixed-methods design. Participants will be 30 adults who have mild to moderate mental health symptoms and not experiencing any issues with pain. The feasibility and acceptability of the interventions will be the primary outcomes. Secondary outcomes will be physiological measures including heart rate variability, interoceptive accuracy and blood pressure. Psychological outcomes, collected preintervention and postintervention, will also be measured by five standardised questionnaires, which include: (1) the Depression, Anxiety and Stress Scale (DASS); (2) the International Positive and Negative Affect Schedule-Short-Form; (3) Acceptance and Action Questionnaire-II; (4) the Self as Context Scale and (5) and the Multidimensional Assessment of Interoceptive Awareness Version 2. Participants will be randomised to one of four intervention groups and receive a single intervention treatment session. These intervention groups are: (1) high-velocity and articulation techniques, (2) soft-tissue massage, (3) craniosacral techniques, and (4) a combination of these three approaches. Mixed design two (preintervention and postintervention) by the four interventions analysis of covariance models will be used to analyse the quantitative data for each quantitative measure. Participants will also be interviewed about their experiences of the study and interventions and a thematic analysis will be used to analyse this qualitative data. This will aid the assessment of the feasibility and acceptability of the study design.

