#### Psychological outcomes

These measures are intended to provide some initial data on the potential utility of the intervention for outcomes such as depression, anxiety and stress, psychological flexibility, and interoceptive awareness. They will be collected during preintervention and postintervention and any changes will be analysed.

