### Sample size

The study will aim to recruit 32 participants. This number of participants is generally deemed sufficient for feasibility studies^48^ and would represent approximately 10% of the sample size required in a full trial.^49^ This sample size also falls within what is practical given the available resources.

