## Methods: assignment of interventions

### Allocation

#### Sequence generation

Thirty-two participants will be randomly assigned to one of the four conditions using a computerised random number generator. Permuted block randomisation will be used to ensure that equal numbers of participants are in each condition. The block sizes will not be disclosed to help ensure concealment and prevent any potential prediction of group allocation. This will be conducted by the principal investigator (PI) of the study [name], while the outcome assessor [name] is blinded to this randomisation process.

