## Statistical methods

### Outcomes

Statistical analysis will be conducted using IBM SPSS (V.27). Means and SD will be reported for demographic data that includes gender, age and ethnicity. For the main analysis, data will first be examined for normality using the Shapiro-Wilk test. If data are skewed, logarithmic transformation will be used, otherwise, analysis will continue without any transformation. HRV data will be preprocessed, and inspected for any potential artefacts, and these will be removed if identified. RMSSD will be calculated on the preprocessed artefact removed data using Kubios V.3.5 (https://www.kubios.com/) via Matlab V.R2021a. IAc will then be calculated using the formula: IAc=1/4 Σ [1−(|recorded heartbeats−counted heartbeats|/recorded heartbeats)]. The psychometrics will be totalled according to the relevant questionnaire instructions and subscales.

The main analysis will comprise of seven separate mixed design two (preintervention and postintervention) by four (AVHT, STM, CST, combination (please see: Interventions section for full details of these interventions.)) analysis of covariance (ANCOVA) models. This will comprise of five separate ANCOVAs for the five psychometrics (DASS, PANAS-SF, AAQ, SACS, MAIA) and another two ANCOVAs for the physiological measures of IAc and HRV (as measured by RMSSD and LF/HF ratio). Covariates will consist of (1) whether participants are currently receiving psychotherapy (yes or no) and (2) whether participants are receiving pharmacological treatment (yes or no). Significant models will be examined further using post hoc Bonferroni tests.

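### The planned 2 × 4 mixed models compare arms on change and do not adjust for the preintervention score; the test is valid, but with eight per arm it loses precision unless the pre-post correlation is very high

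*Protocol article*

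**What the plan says.** Under Statistical methods, Outcomes, the protocol article states: "The main analysis will comprise of seven separate mixed design two (preintervention and postintervention) by four" (the four arms) ANCOVA models. It then fixes the covariates: "Covariates will consist of (1) whether participants are currently receiving psychotherapy (yes or no") and ("2) whether participants are receiving pharmacological treatment (yes or no"). The Concomitant care and Additional outcomes sections name the same two items; the latter enters them only if several participants report such treatment. No section makes the preintervention score a covariate.

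Each outcome is measured once before and once after the session. Of the questionnaires, the Psychological outcomes section says: "They will be collected during preintervention and postintervention and any changes will be analysed". Follow-up of the models is described as: "Significant models will be examined further using post hoc Bonferroni tests". The model term that must be significant is not named.

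On numbers, Sample size says "The study will aim to recruit 32 participants", and Sequence generation says "Permuted block randomisation will be used to ensure that equal numbers of participants are in each condition". These outcomes are secondary; feasibility and acceptability are primary.

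**The concern.** The label ANCOVA suggests baseline adjustment, but here it refers only to the two treatment-status covariates. The preintervention score enters as part of the outcome. With one value before and one after, the arm-by-time interaction is therefore a comparison of mean change between arms.

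This is a choice the article makes, not a detail left to an analysis plan: the model is named and the covariate list is closed. Two things are at stake. One is precision in the arm contrasts, which are the only randomised comparisons of these outcomes because there is no control group. The other is how a contrast should be read once the arms are seen to differ at baseline, which is common with eight per arm. The Objectives include a between-arm hypothesis, that the four interventions give similar improvements in depression, anxiety, stress and negative affect.

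**Working it through.** **Inputs.** 32 participants (Sample size) in four equal arms (Sequence generation): 32/4 = 8 per arm. The abstract instead says "Participants will be 30 adults who have mild to moderate mental health symptoms", which would be 30/4 = 7.5 per arm; 32 is used here. The article gives no power calculation and no r, so there is no planned figure to reproduce and r is shown over a range. Units are SDs, with equal pre and post variance assumed.

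**Step 1: what the interaction tests.** On one simulated data set of 32 with both yes/no covariates, the arm-by-time F of the mixed model and the F from a change-score model with the same covariates were identical: 0.3452 on 3 and 26 df. If the arm main effect were tested instead, it would average pre and post and so halve any effect present only at post, (0 + d)/2.

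**Step 2: variance of a pairwise arm contrast.**
- Change: 2(1−r) × 2/n. At n = 8, r = 0.7: 0.6 × 0.25 = 0.150.
- Adjusted, slope known: (1−r²) × 2/n. The ratio to change is (1−r²)/[2(1−r)] = (1+r)/2.
- Adjusted, slope estimated: with 32 − 4 = 28 within-arm df, the variance is multiplied by 1 + 1/(28−2) = 27/26. At r = 0.7: 0.51 × 0.25 × 27/26 = 0.132, and 0.132/0.150 = 0.88.

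The simulation used 20,000 trials per r, four arms of eight, without the two yes/no covariates. CI half-widths are for one pairwise contrast.

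| r | (1+r)/2 | × 27/26 | Simulated ratio | 95% CI half-width, change → adjusted (SD) |
|---|---|---|---|---|
| 0.3 | 0.650 | 0.675 | 0.680 | 1.20 → 0.99 |
| 0.5 | 0.750 | 0.779 | 0.780 | 1.02 → 0.90 |
| 0.7 | 0.850 | 0.883 | 0.887 | 0.79 → 0.74 |
| 0.8 | 0.900 | 0.935 | 0.937 | 0.64 → 0.62 |
| 0.9 | 0.950 | 0.987 | 0.992 | 0.454 → 0.451 |
| 0.95 | 0.975 | 1.013 | 1.018 | 0.321 → 0.323 |

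Break-even is where (1+r)/2 × 27/26 = 1, that is r = 52/27 − 1 = 0.93. To match the adjusted analysis at 8 per arm, the change analysis would need about 8/0.780 = 10.3 per arm at r = 0.5 and 8/0.887 = 9.0 at r = 0.7.

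**Step 3: chance baseline differences.** The SE of a difference between two arm means at baseline is √(2/8) = 0.50 SD. For a given pair, P(|difference| > 0.5 SD) = 2(1 − Φ(1)) = 32%. By simulation, the largest of the six pairwise differences exceeds 0.5 SD in 75% of randomisations.

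**Step 4: what the change contrast carries over.** Given a baseline difference d, the expected post difference without any effect is r·d, so the change contrast expects r·d − d = −(1−r)d. For d = 0.5 SD this is 0.25 SD at r = 0.5, 0.15 SD at r = 0.7 and 0.05 SD at r = 0.9, in the direction that favours the arm that started worse. The simulated slopes on d were −0.50, −0.30 and −0.10 for change, and 0.00 with the baseline as covariate.

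**The case against.** The strongest reply is that nothing in the plan is invalid. Under randomisation the change contrast is unbiased and the test keeps its error rate. A reader might infer from Step 4 that the planned analysis is biased; that holds only conditional on an observed imbalance, not over repeated randomisations. This part of the reply stands.

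The gain also depends wholly on r. Table 3 puts the post tests straight after a 30-minute session, so r could be high for trait-like questionnaires such as the AAQ-II, SACS and MAIA-2. It may be lower for affect, HRV or IAc. Near r = 0.9 nothing is gained. The large-sample ratios (1+r)/2 flatter the adjustment at this size, and the 75% is for the most extreme of six pairs. All of this stands and limits the size of the point.

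A reader might also infer that the arm contrasts are declared inputs to the next trial. The abstract's Discussion does not say so. It ties the future trial to the assessment of feasibility and acceptability, and mentions effect sizes separately, as preliminary evidence of benefit. Nor is the planned comparison one of raw change: it is adjusted for two covariates and may be log-transformed. The article concedes low power openly, and the repeated-measures time effect suits the hypotheses that HRV and IAc will improve.

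What the reply does not remove is the asymmetry. r is unknown beforehand; adjustment gains clearly at low to moderate r and costs almost nothing at high r.

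**Conclusion.** The point holds as one of efficiency and of reading the contrasts conditionally on baseline, for secondary outcomes. It is not one of validity and does not touch the primary outcomes. The planned arm-by-time test compares arms on change and omits the outcome's own baseline from a closed covariate list. Adjustment would cut the variance of an arm contrast by about 22% at r = 0.5, 12% at 0.7, 6% at 0.8 and 1% at 0.9, and would raise it by 1 to 2% at 0.95.

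The arm contrasts stay imprecise either way: at r = 0.7 the CI half-width is still about 0.74 SD, against which a 0.15 SD carry-over is modest.

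These figures assume eight per arm with complete data, equal pre and post variances, a common slope, and an r that the article does not give. The equivalence with change applies to the arm-by-time term, which the article does not name as the one tested.

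**What to change.** In Statistical methods, Outcomes, separate the two questions.

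- **Between arms** (including the hypothesis of similar improvements): model the postintervention score on arm, the centred preintervention score of the same outcome, and the two planned covariates. Report adjusted arm differences with 95% CIs. If a log transformation is used, apply it to both scores.
- **Over time** (HRV and IAc): keep the pre-post mean change as planned.

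State that the arm term of the first model is the one followed up by the Bonferroni tests.

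The cost is a wording change, different SPSS syntax, one residual degree of freedom (26 to 25 with both covariates) and a trivial loss if r is about 0.95. It uses only data that the plan already collects; the section on analysis population and missing data already requires preintervention data for inclusion.

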### Interventions

Participants will receive one of four interventions based on osteopathic techniques. All four interventions will consist of a single session lasting approximately 30 min. The interventions are being delivered by two male osteopaths, one with 17 years of practice experience and one with 3 years of practice experience. The interventions will be as follows: (1) articulation and HVT techniques, (2) STM, (3) CST and (4) a combination of all three techniques. A summary of the intervention protocols can be found in table 1.

**Table 1 T1:** Summary of the four intervention protocols and procedures

For all	30 min appointment Clinical findings, intervention, consent and adverse events (separate form to use if they do) recorded in participant individual form	Duration
Articulation/HVT group	Observation+AROM (standing or sitting)+clinical examination for SD (sitting, prone or supine) Techniques: SD found: HVT to the area unless contraindicated (info on BP/HA) No SD found: HVT TSp and ribs Articulation of hips in extension	10 min 20 min
Soft tissue group	Full body, slow and superficial Prone: upper/mid/lower back upper buttocks hamstrings calves Supine: Neck incl. suboccipital muscles Shoulders Pectoral muscles Arms Quadriceps Feet	15 min 15 min
Cranial group	Looking for stiffness, asymmetry and tenderness on: Sacrum Head Dysfunction found: myofascial release technique (10 min/area); if no dysfunction found: functional techniques applied to each area (10 min/area) 3. CV4	10 min 10 min 10 min
Combined group	Observation+AROM+clinical exam for SD HVT TSp Soft tissue upper and lower back prone CV4 and suboccipital release	9 min 7 min 7 min 7 min

AROM, active range of movement; BP, blood pressure; CV4, Compression of the Fourth Ventricle technique; HA, headache; HVT, high velocity thrust techniques; SD, somatic dysfunction; TSp, thoracic spine.

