### Concomitant care

Participants will be asked at preintervention if they are receiving any drug treatment for mental health (eg, antidepressants), or psychotherapy (eg, cognitive behavioural therapy). Participants will not be excluded on this basis, but these will be factored into the main statistical analysis as covariates.

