#### Additional outcomes

Demographic information will also be collected from participants relating to their gender, age and ethnic background. Although participants will have been screened for chronic pain, they will be asked whether they are currently or have recently been experiencing any neck pain or headaches. This is to inform the clinician about any problematic body areas, which may, therefore, be avoided in the intervention. The participants should be presenting as pain-free due to the initial screening process, but this is still a necessary safety measure. Participants will be excluded from the analysis if they present with neck pain or headaches.

Participants will also be asked whether they are currently receiving any mental health treatment. They will be asked whether they are currently taking any antidepressants or other related prescribed medication for mental health issues. Participants will also be asked whether they have recently attended or are currently attending any form of talking therapy or other psychotherapy. Participants’ prescription medication or psychotherapy status will not exclude them from the study. However, this will again be entered as a covariate if several participants report that they are receiving these psychological treatments.

Lastly will be the noting of any adverse events that occur during the intervention or study period. These will be filled out by the practitioner using the AERF and collected by the researcher if occurring during the intervention. If participants contact the researcher after the intervention regarding an adverse event, then this will be logged by the researcher.

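### The 2×4 mixed model compares arms on change scores and leaves the baseline score unadjusted, and the protocol gives two conflicting rules for its treatment covariates

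*Protocol article*

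**What the plan says.** Under Statistical methods, Outcomes, the main analysis is "seven separate mixed design two (preintervention and postintervention) by four" ANCOVA models, the four levels being the intervention arms. The adjustment set is stated without conditions: "Covariates will consist of (1) whether participants are currently receiving psychotherapy (yes or no) and (2) whether participants are receiving pharmacological treatment". The preintervention score is one of the two levels of the time factor and is not among the covariates.

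Concomitant care agrees that the two treatment variables always enter: "these will be factored into the main statistical analysis as covariates". Additional outcomes sets a different rule for the same variables: "this will again be entered as a covariate if several participants report that they are receiving these psychological treatments". It does not say how many participants count as several.

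Under Interventions, sessions are "delivered by two male osteopaths, one with 17 years of practice experience and one with 3 years of practice experience". Practitioner is not in the model, and the article does not say how sessions are divided between the two. On size, "The study will aim to recruit 32 participants", in four equal arms.

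**The concern.** The preintervention score is collected from everyone and is usually the strongest predictor of the postintervention score. A model that only subtracts it uses that information less well than one that regresses on it, and it does not correct for arms that start at different levels. With eight per arm such differences will be common. The article concedes low power and names effect sizes as a product meant to inform a later trial, so imprecision in between-arm estimates reaches that use directly.

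The covariate rule raises a different issue. If one section fixes the covariates and another makes them depend on how many participants report treatment, the protocol describes two models and the choice between them is made after the data are seen.

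**Working it through.** **Inputs.** N = 32 in four equal arms, so 32/4 = 8 per arm. (The Abstract says "Participants will be 30 adults who have mild to moderate mental health symptoms"; 30/4 = 7.5 does not divide equally. That is a separate inconsistency.) The article gives no pre-post correlation, SD, alpha or target effect, and 32 rests on convention and resources, so there is no power calculation to reproduce. Assumptions here: correlation r from 0.3 to 0.9, equal pre and post SDs (set to 1), two-sided 95% intervals.

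**Step 1: the planned test is a change-score test.** In a check dataset of 32 with both yes/no covariates, the time-by-arm F from the mixed model and the arm F from a model for post minus pre were both 0.3779 on 3 and 26 degrees of freedom (32 − 4 − 2 = 26).

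**Step 2: residual variance for between-arm contrasts.**
- Change score: 2(1 − r).
- Post score adjusted for baseline: 1 − r².
- Ratio: (1 − r²) / [2(1 − r)] = (1 + r)/2.

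**Step 3: interval for a difference between two arms.** The half-width is t × √(variance × 2/8), with t = 2.0555 on 26 df for change scores and 2.0595 on 25 df with baseline added. The baseline-adjusted column also carries a factor of about 1.02 for estimating the slope.

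| r | variance ratio | half-width, change score (SD) | half-width, baseline-adjusted (SD) |
|---|---|---|---|
| 0.3 | 0.65 | 1.22 | 1.00 |
| 0.5 | 0.75 | 1.03 | 0.91 |
| 0.7 | 0.85 | 0.80 | 0.75 |
| 0.9 | 0.95 | 0.46 | 0.46 |

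Example at r = 0.5: 2.0555 × √(1.0 × 0.25) = 1.03; 2.0595 × √(0.75 × 0.25) × 1.02 = 0.91.

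**Step 4: chance imbalance.** The baseline difference between two arms of eight has standard deviation √(2/8) = 0.5 SD. Given a baseline gap d, and no treatment difference, the expected difference in change is −(1 − r)d. At r = 0.5 and d = 0.5 that is 0.25 SD, arising from the starting levels alone.

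**Step 5: overall pre-post change.** The SE of the mean change over 32 people is √[2(1 − r)/32], which at r = 0.5 is √(1/32) = 0.177 SD. A model with mean-centred baseline as covariate would report √[(1 − r²)/32] = √(0.75/32) = 0.153 SD, because it treats the sample's baseline mean as fixed. The true sampling error is not reduced, so 0.153 is too small.

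**Step 6: the covariate rules side by side.** Concomitant care and Statistical methods enter both variables always. Additional outcomes enters them only on a condition with no threshold. These cannot both be followed if few participants report treatment. Precision is hardly involved: in simulation, two covariates unrelated to outcome widen the change-score half-width from 1.02 to 1.06 SD at r = 0.5, about 4%.

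**The case against.** The strongest reply is that the trial's directional hypothesis, that HRV and interoceptive accuracy improve, concerns overall pre-post change with no control group, and that a pre/post mixed model is a legitimate way to test it. That stands. Baseline adjustment does nothing for that question and, applied carelessly, understates its SE (step 5). The gain is confined to between-arm contrasts, on which the article predicts only similar improvements.

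It also stands that the gain depends on r. Post-tests follow a session of about 30 minutes, and some scales may behave like traits, so high correlations are plausible. It would be wrong to say that the planned model is less precise at every correlation below 1, because at this sample size the advantage is used up near 0.9.

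Stronger readings that the document does not support:
- *The model adjusts for the wrong things.* Concurrent psychotherapy and medication are reasonable covariates and should stay.
- *The main model's covariates depend on the data.* The Statistical methods section fixes them; only Additional outcomes makes them conditional. That condition concerns reported treatment, not outcomes, and the analyst is blind to allocation.
- *Practitioner is confounded with technique, or omitting practitioner wastes precision.* The assignment of sessions is not stated, so confounding can be neither shown nor excluded. In simulation at r = 0.5, adding a practitioner term to the baseline-adjusted model moves the half-width from 0.93 to 0.95 SD if practitioners do not differ. It breaks even at about 5% of residual variance and reaches 0.85 (from 0.94) only at 20%.
- *Covariate coding distorts the time effect.* The article does not state numeric coding or centring, and need not. The point matters only for specifying the overall-change estimate clearly.

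**Conclusion.** Two points hold. First, between-arm comparisons are change-score comparisons that leave baseline imbalance between arms of eight unadjusted. Baseline adjustment would reduce their residual variance by 35%, 25% and 15% at r = 0.3, 0.5 and 0.7, with essentially no net gain near 0.9. These figures rest on assumed correlations and equal pre and post SDs. Second, the protocol contradicts itself on whether the two treatment covariates always enter. That is a prespecification fault, separate from precision.

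Both are worth correcting. Neither threatens the study: these are secondary outcomes in a feasibility trial that admits low power, and the effect is on the between-arm effect sizes carried forward.

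**What to change.** - **Between-arm contrasts:** model the postintervention score on arm, with its own preintervention score and both treatment covariates always included.
- **Overall pre-post change:** estimate it from the change scores, with the two yes/no covariates mean-centred and without baseline as a covariate. The estimate is then the average change in the sample, with a correct SE.
- **Covariate rule:** delete the conditional clause in Additional outcomes so that it agrees with Concomitant care and Statistical methods.
- **Practitioner:** record which osteopath treated each participant and use it, at most, in a sensitivity analysis.

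The cost is one degree of freedom for baseline (26 to 25) and a change of syntax. No extra participants, visits or measurements are needed, only a note of who delivered each session.

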**Discussion:**

This study will assess the feasibility and acceptability of conducting osteopathic interventions for improving mental health outcomes. The results from this will help to inform the development of a future randomised controlled trial. The study will also produce original data which could provide preliminary evidence of whether osteopathic approaches are of benefit to individual’s mental health in the form of effect sizes, even if they are pain-free.

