**Trial registration number:**

NCT05674071.

STRENGTHS AND LIMITATIONS OF THIS STUDYThis study will investigate the utility of osteopathic techniques for improving mental health, in the absence of any existing pain.The techniques being compared are based on previous literature and evidence.Due to this being a feasibility study, only a small number of participants are being recruited which will lead to low statistical power of the results.As the study is focused on comparing four interventions in a feasibility setting, there will be no control group comparison.

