### Trial design

This is a feasibility study, which will use an explanatory sequential mixed-methods approach. In this approach, the quantitative aspect forms the first part of the study, followed by a qualitative aspect to help provide further explanation and depth.^32^ For the quantitative aspect, the study will use a parallel, randomised design with an equal proportion of participants allocated to each of the four conditions. The qualitative aspect will be completed by interviewing the participants of the intervention and the practitioner delivering them.

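### Arm contrasts are examined only after a significant model, so any contrast carried forward because it passed that gate would be inflated

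*Protocol article*

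**What the plan says.** Under Statistical methods, Outcomes, the article describes the quantitative analysis: "The main analysis will comprise of seven separate mixed design two (preintervention and postintervention) by four" ANCOVA models, with psychotherapy and drug treatment as yes/no covariates. The arm-by-arm step follows: "Significant models will be examined further using post hoc Bonferroni tests". The text does not say which term (time, arm, or time by arm) makes a model significant. It commits to means and SDs for the demographic data.

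The abstract's Discussion says the results will help develop a future randomised trial. It adds that the data could give preliminary evidence of benefit to "mental health in the form of effect sizes, even if they are pain-free". The strengths and limitations box concedes that "only a small number of participants are being recruited which will lead to low statistical power of the results".

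On size, the Sample size section says "The study will aim to recruit 32 participants", while the abstract says "Participants will be 30 adults who have mild to moderate mental health symptoms". Trial design specifies "an equal proportion of participants allocated to each of the four conditions". Under Objectives, the four interventions are expected to bring similar improvements in depression, anxiety, stress and negative affect.

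**The concern.** The stated product is a set of estimates to inform a later trial, but the stated route to arm comparisons is a significance test. With about 8 per arm, an arm difference usually has to be large in the sample before such a test is significant. Contrasts that are looked at, remembered or taken forward because they passed are therefore selected for being large.

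The article's own expectation sharpens this. If the four arms really do improve alike, a gate on arm differences opens only by chance. If the gate stays closed, the described analysis offers no arm differences or intervals against which to judge the similarity claim.

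At stake is what the next team uses. Estimates of all contrasts, with their imprecision, are useful. A few contrasts chosen for significance could mislead them about the size of a difference or about which technique looks best.

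**Working it through.** **The plan's own figure.** The target of 32 rests on a rule of thumb, about 10% of a full trial: 32/0.10 = 320, or 80 per arm. No alpha, power, effect size, SD or pre-post correlation is given, so 32 cannot be rebuilt from a power calculation.

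**Inputs from the article.** Four equal arms and N = 32, so n = 8 per arm (the abstract's 30 gives 7.5). Error df are 32 − 4 = 28, or 26 with the two covariates. There are 4 × 3/2 = 6 pairwise contrasts.

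**Assumptions not in the article.** Two-sided alpha 0.05; equal variances; the gate is a test of arm differences in change; differences are in SDs of change; true differences of 0.2 to 1.0 SD.

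**Step 1: the pairwise cut-off.** The smallest Bonferroni-significant difference is t(1 − 0.05/12; 28) × √(2/8) = 1.42 SD. With covariates it is 1.43, and at N = 30 it is 1.47 to 1.48. In baseline-SD units, multiply by √(2(1 − ρ)): 1.68, 1.42, 1.10 or 0.90 for assumed pre-post correlations ρ of 0.3, 0.5, 0.7 or 0.8.

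**Step 2: the model gate.** F(0.95; 3, 28) = 2.947. The largest contrast at which F can just be significant is at least √(3F/n) = √(3 × 2.947/8) = 1.05 SD. The gate can thus open well below 1.42 SD. In the simulations below, once it opened, about 75% to 84% of the six contrasts were under 1.42 SD.

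**Step 3: inflation.** 400,000 trials were simulated per setting (n = 8, df 28). In three patterns of means, one pair was extreme, one arm differed, or two arms differed from two; the last was run only at 0.3, 0.5 and 0.8. Inflation is the average estimate among trials that pass, divided by the true difference; the last column uses absolute size.

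| True difference (SD of change) | Model gate opens | Inflation, model gate alone | Inflation, gate plus Bonferroni |
|---|---|---|---|
| 0.2 | 6% | 3.1–3.2 | 8.2 |
| 0.3 | 7–9% | 2.6–2.9 | 5.5 |
| 0.5 | 11–17% | 2.0–2.4 | 3.4 |
| 0.8 | 21–40% | 1.5–1.8 | 2.2 |
| 1.0 | 32–46% | 1.4–1.6 | 1.8 |

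With no true difference the gate opens in 5% of trials per model.

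**Step 4: without the filter.** When every contrast is estimated, the averages are 0.31, 0.51 and 0.82 for true values of 0.3, 0.5 and 0.8. That is nearly unbiased (about 3% small-sample bias).

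**Step 5: the other reading of the gate.** If the significant term is time, the gate needs an observed standardised change of about t(0.975; 28)/√32 = 2.048/5.657 = 0.36. That does not select on arm differences. Carrying forward only Bonferroni-significant pairs still would.

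**Step 6: precision of an ungated contrast.** The 95% half-width is t(0.975; 28) × √(2/8) = 2.048 × 0.5 = 1.02 SD of change.

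**The case against.** The strongest reply is that a rule about testing is not a rule about reporting. The article makes the post hoc tests conditional; it does not say that arm means, changes or effect sizes are withheld when a model is not significant. The effect sizes in the abstract carry no significance condition and are not stated to be between-arm; pre-post benefit is a natural reading. The de-identified dataset and the analysis syntax are promised for open release, so anyone could compute every contrast. An overall test followed by corrected pairwise tests is conventional, the primary outcomes are feasibility and acceptability, and low power is disclosed.

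Most of this stands, and it rules out three inferences a reader might draw:

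- *Effect sizes will be seen only above about 1.4 SD.* That figure is the pairwise Bonferroni cut-off. The written gate is the model test, which can open with a largest contrast of about 1.05 SD.
- *The estimates will overstate the truth by a fixed multiple, such as two- to five-fold.* That needs an assumed true effect, the added Bonferroni filter and selective use of what passes.
- *The next trial will be undersized as a result.* No section says it will be sized on significant contrasts, or that a technique will be chosen from them.

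Nor is it a fault that the article lists no intervals or outcome SDs; an article may leave that detail to a fuller document. What the reply does not remove is that the condition is written down, its triggering term is undefined, and it works against the stated use of the results. Open data let others compute the contrasts but do not commit the authors to reporting them or planning from them.

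**Conclusion.** The point holds in a conditional form. Arm contrasts are gated on significance in a study of about 8 per arm that acknowledges low power and promises effect sizes for a later trial. Any contrast carried forward because it passed a gate on arm differences would be inflated. The direction is secure, but the multiple is only illustrative: it rests on the alpha, change-SD units, gate and true differences assumed above, none of which the article supplies. If time is the gating term, the gate itself adds no such selection. This is a weakness in how the secondary results are fixed for later use. It does not show that estimates will be withheld, and it does not touch the feasibility and acceptability outcomes.

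**What to change.** Amend Statistical methods, Outcomes as follows:

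- Remove model significance as the condition for the arm contrasts.
- For every outcome, whatever the p-value, report each arm's mean change and all six arm differences with 95% confidence intervals, together with the SD and the pre-post correlation.
- State that the next trial will not be sized from contrasts selected for significance.
- If a gated test is kept alongside the estimates, name the model term it refers to.

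No new data are needed. The cost is wording, larger tables, and intervals that are visibly wide, at about ±1.0 SD of change for each contrast.
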